**3.4. Definition of prevalence and incidence**

Prevalent STI/BV infections will be defined by diagnosis at the baseline visit. Infections will be coded as positive, negative, or missing/not classifiable/not collected or asked. Positive syphilis cases will be further categorized based on rapid plasma regain (RPR) titer testing as high titer active infection, low titer infection or unknown RPR titer infection.

Infections defined as:

Chlamydia: Positive: Positive nucleic acid amplification test (NAAT), enzyme immunoassay (EIA), or hybrid capture test

Gonorrhea: Positive: Positive NAAT, or culture

Trichomoniasis: Positive: Positive NAAT, InPouch culture, or wet mount

HSV-2: Positive: Positive type-specific serologic test

BV: Positive: Nugent score (≥7), Ison-Hay grade (≥Grade III), or Amsel criteria (≥ 3 criteria)

Syphilis (see Appendix table 4):

Positive (overall): positive RPR AND positive treponemal test (*Treponema pallidum* hemagglutination assay [TPHA], *Treponema pallidum* particle agglutination assay [TPPA] or Determine TP rapid test)

With subclassification based on RPR titer testing:

Positive, high titer active infection: positive RPR with a titer ≥1:8 AND positive treponemal test

Positive, low titer infection: 1) positive RPR with a titer <1:8 AND positive treponemal test

Positive, unknown RPR titer infection: 1) positive RPR with missing titer AND positive treponemal test

Negative: 1) negative RPR or 2) positive or missing RPR AND negative treponemal test

Missing: 1) positive RPR AND missing treponemal test or 2) missing RPR AND missing or positive treponemal test

For estimation of incident infections, individual study protocols will be reviewed to assess time frames of repeat STI testing, types of laboratory tests used, treatment information for curable STIs. For chlamydia, gonorrhea, trichomoniasis, and HSV-2, incident infection will be defined as the first positive laboratory test following a previously negative result for the infection. For trichomoniasis, incidence estimations will be limited to those studies where *T. vaginalis* testing was done using InPouch or NAAT. For syphilis incidence, using the categories defined above, an incident infection will be defined as:

1. participants who are negative at baseline who are diagnosed at a follow-up visit with a positive infection OR

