2. participants who had a positive, low titer infection at baseline who are diagnosed at follow-up with a positive, high titer active infection with a 4-fold increase in titer.

For all analyses, time of infection will be estimated as the midpoint between the last negative test and the first positive test.

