**Table 4. Categorization of syphilis results**

| 0 | | RPR Results | | | | |
| --- | --- | --- | --- | --- | --- | --- |
|  |  | **Positive & titer ≥1:8** | **Positive &**  **titer <1:8** | **Positive &**  **missing titer** | **Negative** | **Missing** |
| Treponemal test Results | **Positive** | Positive, high titer active | Positive, low titer infection | Positive, unknown titer infection | Negative | Missing |
|  | **Negative** | Negative | Negative | Negative | Negative | Negative |
|  | **Missing** | Missing | Missing | Missing | Negative | Missing |

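### Syphilis incidence holds women already treponemal-positive at baseline to two different standards, so earlier infection can be counted as incident, and no planned sensitivity analysis tests this

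*Protocol*

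**What the plan says.** Section 3.4 of the protocol defines the syphilis categories, and incidence uses the same categories.

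- **Negative.** "Negative: 1) negative RPR or 2) positive or missing RPR AND negative treponemal test". A negative RPR is enough, whatever the treponemal result.
- **Table 4.** For a positive treponemal test, the row reads "Positive, high titer active | Positive, low titer infection | Positive, unknown titer infection | Negative | Missing", the columns being RPR at or above 1:8, below 1:8, positive without titer, negative, and missing. Treponemal-positive with RPR-negative is therefore Negative. RPR-negative with a missing treponemal test is Negative too.
- **Positive.** "Positive (overall): positive RPR AND positive treponemal test", with no minimum titer. The subclass of unknown titer ("positive RPR with missing titer AND positive treponemal test") is still Positive. The word active is kept for titers of 1:8 or more.
- **Incidence rule 1.** "participants who are negative at baseline who are diagnosed at a follow-up visit with a positive infection".
- **Incidence rule 2.** Women with a low-titer infection at baseline must be "diagnosed at follow-up with a positive, high titer active infection with a 4-fold increase in titer".

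Section 3.4 dates infection at the midpoint between the last negative and the first positive test. Syphilis incidence is an Objective 2 outcome (sections 2, 3.2 and 3.3), to be reported by region, population type, age and time period.

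**The concern.** Two groups of women enter follow-up with a positive treponemal test: those with a negative RPR and those with a low-titer RPR. A treponemal test that was already positive cannot supply new evidence of infection, so in both groups the case rests on the RPR. Rule 2 asks for a large change to an active-level titer. Rule 1 asks for any reactivity at all, and accepts a result with no titer.

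If some RPR-negative women with earlier infection later show a weakly reactive RPR without being infected again, rule 1 counts them as new cases and dates the infection within follow-up. The syphilis incidence rate would then be too high by an amount that depends on how many such women are in the at-risk set. That share may vary between studies, so comparisons between strata could also be affected.

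**Working it through.** **Step 1. Do the text and Table 4 agree?** The protocol states no figure to reproduce here. Coding the section 3.4 definitions and comparing them with Table 4 gives agreement in 15 of 15 cells. The problem is therefore not a slip between text and table.

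**Step 2. Apply the two rules to treponemal-positive women.** The treponemal test is taken as again positive at follow-up, and the 4-fold condition is read as at least 4-fold. Entries show whether the woman is counted as incident.

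| Baseline RPR | Rule | 1:1 | 1:2 | 1:4 | 1:8 | 1:16 | 1:32 | Positive, no titer |
|---|---|---|---|---|---|---|---|---|
| Negative | 1 | yes | yes | yes | yes | yes | yes | yes |
| 1:1 | 2 | no | no | no | yes | yes | yes | no |
| 1:2 | 2 | no | no | no | yes | yes | yes | no |
| 1:4 | 2 | no | no | no | no | yes | yes | no |

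The rules part at follow-up titers of 1:1, 1:2, 1:4 and missing: always incident from a negative baseline RPR, never from a low-titer one. A move from negative to 1:1 counts. A move from 1:1 to 1:4 is a 4-fold rise (4 / 1 = 4) and does not count, because it stays below 1:8.

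**Step 3. Does another analysis vary this definition?**

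- Section 3.6 says syphilis estimates will be evaluated by diagnostic test type and points to section 5.3.
- Section 5.3 lists diagnostic-criteria analyses for chlamydia, gonorrhea and BV only.
- The Table 5 sensitivity row on diagnostic criteria names syphilis but covers prevalence.

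None of these changes what counts as an incident case.

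**Step 4. Possible size, on assumed inputs.** Let s be the share of baseline-negative women who are treponemal-positive, r the rate per 100 person-years at which they turn RPR-positive without new infection, and I the true incidence per 100 person-years, taken as equal in all at-risk women. Then, ignoring the small effect of censoring,

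observed rate = I + s × r, and relative inflation = s × r / I.

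The protocol gives none of the three. The ranges assumed are s = 2% to 10%, r = 1 to 10 and I = 1 to 4.

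- Smallest excess: 0.02 × 1 = 0.02. With I = 4, the inflation is 0.02 / 4 = 0.5%.
- Middle: 0.05 × 5 = 0.25. With I = 2, the observed rate is 2.25 and the inflation is 0.25 / 2 = 12.5%.
- Largest excess: 0.10 × 10 = 1.0. With I = 1, the inflation is 1.0 / 1 = 100%.

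The range runs from negligible to a doubling, so it illustrates the mechanism and does not estimate the bias.

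**The case against.** The strongest defence is that the two rules start from different states. Rule 2 concerns women who already meet the case definition, in whom a second infection can be shown only by a rise in titer. Rule 1 concerns women who do not meet the definition and later do. One case definition at baseline and follow-up is a coherent choice, and rule 2 says nothing about RPR-negative women. This stands in part: the rules can be applied without logical conflict. It does not explain why a 4-fold rise from 1:1 to 1:4 is rejected while a first weak reaction, or a reaction with no titer, is accepted in a woman with the same treponemal result.

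Three further points stand.

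- **Some of these conversions may be true infections.** A reader might infer that every treponemal-positive woman counted at a low titer is a false case. The documents do not support that, because the definition cannot separate reinfection from earlier infection.
- **The affected group may be small or unidentifiable.** Table 3 names the syphilis tests but not whether RPR-negative samples had a treponemal test, and it is marked as still to be updated. Section 3.2 requires syphilis testing at least every 6 months. Table 3 clearly shows such a schedule only for studies 3a/b and 6, and possibly for study 13.
- **Changing the primary rule has its own cost.** A stricter rule applied only where baseline treponemal results exist would make the incidence definition depend on each study's laboratory algorithm, adding artificial heterogeneity to a pooled analysis.

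Section 3.4 also promises a review of each study's test timing, laboratory tests and treatment information. That is useful, but it fixes no alternative case definition.

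**Conclusion.** The inconsistency is real and follows from section 3.4 and Table 4 alone. Women with treponemal reactivity at baseline are counted as incident at any RPR titer if their baseline RPR was negative, but only at 1:8 or more with a 4-fold rise if it was low-titer. Earlier infection can therefore be counted as incident, and the syphilis rate can be biased upward. That last step assumes that some treponemal-positive, RPR-negative women turn weakly RPR-positive without new infection, which the protocol neither states nor excludes.

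The size cannot be computed from the document; the assumed ranges in the working set no bound. A reader might also infer that the contrast between higher-risk and clinic/community populations is distorted because past infection is commoner in higher-risk women. The protocol gives no treponemal results by population type, so this remains a possibility to be checked. The finding justifies a pre-specified sensitivity analysis, and does not by itself justify replacing the primary definition.

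**What to change.** Keep rule 1 as the common definition across studies where baseline treponemal status is unknown. Then pre-specify, in section 5.3 and Table 5, a syphilis-incidence sensitivity analysis with two parts.

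1. **All studies:** count only incident cases with a high titer (at least 1:8). This needs no baseline treponemal result.
2. **Studies with baseline treponemal results for RPR-negative women:** remove women known to be treponemal-positive and RPR-negative from the rule 1 at-risk set, or hold them to the rule 2 titer standard. For the second option, state how a 4-fold rise is read when the baseline RPR is non-reactive. Compare with the main analysis in the same studies, so that a change in study mix is not mistaken for an effect of the definition.

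Report incident cases by titer class (high, low, unknown), overall and by population type, and state for each study whether RPR-negative samples had a treponemal test. Table 5 will need a syphilis-incidence row, since its incidence rows name only chlamydia, gonorrhea and HSV-2.

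The cost is protocol wording, recoding of existing results and a little more analysis. In these analyses some true low-titer or missing-titer infections, including reinfections, will not be counted, so they show how far the rate depends on the rule and do not give a corrected rate.

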**3.5. Censoring for incidence calculation**

Study participants will be censored at the first time they are documented as diagnosed with selected STI or at the end of the study or at the last follow-up visit where STI testing was done. If resources allow and data are available/complete, a sensitivity analysis will be conducted to estimate incidence of recurrent STIs; analyses will apply appropriate statistical methods to account for non-independence of subject-specific observations.

**3.6. Stratification of prevalence and incidence estimates**

Because of possible heterogeneity in STI/BV prevalence and incidence among studies, for each STI/BV we plan to stratify results according to pre-specified characteristics. (See Supplemental Tables 1.1 – 1.2 for proposed stratifications for prevalence estimates and Supplemental Tables 2.1 – 2.2 for proposed stratifications of incidence estimates.) We will first stratify according to the study-level characteristics for region and population type. Within these strata (region and population type), we will then explore STI/BV prevalence and STI incidence according to individual-level characteristics, including: age, time period of enrolment, and pregnancy status (prevalence estimates only). Additional stratifications, such as by sexual behaviors including number of recent sexual partners, could be explored if resources allow. Additionally, diagnostic test used can influence observed prevalence. For BV, those diagnosed by Nugent or Ison-Hay criteria will be evaluated separately from those diagnosed by Amsel criteria only. A sensitivity analysis will be conducted to determine if the estimates remain robust if Amsel only results are included with the Nugent/Ison-Hay results (see section 5.3). For chlamydia, gonorrhea, syphilis and trichomoniasis, estimates will be evaluated by diagnostic test type to investigate robustness of estimates (see section 5.3).

Region (based on geographical location of the study) will be defined as South Africa, Eastern Africa (Kenya, Uganda, Tanzania, Rwanda), or Southern Africa (Zambia, Zimbabwe, Malawi, Botswana). Population types (based on overall study population enrolled) will be defined as higher-risk or clinic/community-based populations. Higher-risk populations include studies where participants were recruited from bars or other recreational facilities like guesthouses and hotels, or were women who engage in transactional sex. Clinic/community-based populations include participants recruited in a clinic setting, such as a family planning/reproductive health clinic, as well as studies where participants were recruited from the general population or community. Some studies in the HC-HIV meta-analytic dataset recruited HIV-negative partners in HIV-discordant couples. Although these participants may be at higher risk for HIV transmission than the general population, their risk for STI/BV may be similar to clinic/community-based populations given that they are in a stable relationship. These studies will initially be analyzed separately, STI/BV specific estimates reviewed, and if appropriate (based on comparison with estimates from other populations), will be included in either the higher-risk strata or the clinic-based strata. If not appropriate, estimates from these studies will be presented separately. See Appendix Table 1 for proposed classifications of studies according to these two characteristics.

Time period, age, and pregnancy status will be based on individual participant characteristics. Time period will be categorized as participants whose baseline data were collected prior to 2002 (“earliest” time period), participants whose baseline data were collected during 2003 to 2006 (“later” time period), and participants whose baseline data were collected in 2007 or later (“latest” time period). The categorization of time periods may be adjusted if necessary based on available sample size. Age will be categorized as 15-49 years, 15-24 years, 25-49 years, and if possible given sample size, 15-19 years, and 20-24 years. The categorization of age may be adjusted if necessary based on available sample size. Pregnancy status will be based on pregnancy status at baseline, either self-reported or by pregnancy test.

To the extent possible given sample size, prevalence and incidence estimates will be cross-stratified by various characteristics.

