**3.7 Estimation of STI co-infection**

To broadly evaluate the prevalence and incidence of STI co-infection for the STIs/BV under consideration, the percentage of participants co-infected with two STIs/BV will be estimated. STI co-infection estimates will be estimated by population type (based on overall study population enrolled) defined as higher-risk or clinic/community-based populations and within population type by age group. For co-infection estimates, the denominators will be limited to those participants who were tested for the two STIs under consideration. See Supplemental Table 3. If resources allow, additional co-infection analyses will estimate the number of STIs/BV diagnoses received by participants (e.g., 0, 1, 1-2, 3+).

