**5.2.1 Two-stage meta-analysis**

We will use two-stage meta-analysis as our primary approach to examine prevalence and incidence estimates. Using this method, participants in each study are compared directly only with other participants in the same study. The two-stage method is well suited to assess between study heterogeneity. While the method is less suitable for identifying prognostic factors (due to the different sets of covariates measured across datasets), it is possible to assess effect modification.

In the first stage, IPD in each study are analyzed separately to obtain summary statistics. We will use binomial regression models to estimate prevalence estimates for each selected STI/BV and Poisson regression to estimate the incidence for each selected STI.

If appropriate, the second stage is to use standard meta-analysis techniques to combine the summary measures to give an overall estimate of prevalence and incidence across studies by population-type. The decision to combine results and conduct further analyses using random and/or fixed effect models depends on the level of between-study heterogeneity.

The same approach will be used to estimate prevalence and incidence for each stratum of interest based on region, population type, age, pregnancy status, and time period of the study.

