**Table 5. Planned tables and forest plots**

| **Analysis objective** |  | **Meta-analysis output/presentation** | | | |
| --- | --- | --- | --- | --- | --- |
|  | **Analysis population** | **Baseline table** | **Heterogeneity evaluation** | | **One-stage stratified analysis and two-stage random effect analysis** |
|  |  |  | **I^2^** | **Forest plot** |  |
| **Primary** |  |  |  |  |  |
| **To evaluate the prevalence of selected STIs/BV: gonorrhea, chlamydia, syphilis, trichomoniasis, HSV-2, and/or BV** | **All studies** | **√** | **√** | **√** | **√** |
|  | **Region**: South Africa, Eastern Africa, Southern Africa | **√** | **√** |  | **√** |
|  | **Population type**: higher-risk or clinic/community-based populations | **√** | **√** |  | **√** |
|  | **Time period**: baseline data were collected prior to 2002, during 2003 to 2006 2007 or later | **√** | **√** |  | **√** |
|  | **Age**: 15-49 years, 15-24 years, 25-49 years | **√** | **√** | **√** | **√** |
|  | **Pregnancy**: pregnancy status at baseline | **√** | **√** |  | **√** |
|  | **Cross-stratum (Region, Population type, Time period, Age, Pregnancy)**^1^ | **√** | **√** |  | **√** |
| **To evaluate the incidence of selected STIs: chlamydia, gonorrhea, and HSV-2** | **All studies** | **√** | **√** | **√** | **√** |
|  | **Region**: South Africa, Eastern Africa, Southern Africa | **√** | **√** |  | **√** |
|  | **Population type**: higher-risk or clinic/community-based populations | **√** | **√** |  | **√** |
|  | **Time period**: baseline data were collected prior to 2002, during 2003 to 2006 2007 or later | **√** | **√** |  | **√** |
|  | **Age**: 15-49 years, 15-24 years, 25-49 years | **√** | **√** | **√** | **√** |
|  | **Pregnancy**: pregnancy status at baseline | **√** | **√** |  | **√** |
|  | **Cross-stratum (Region, Population type, Time period, Age, Pregnancy)**^1^ | **√** | **√** |  | **√** |
| **Secondary** |  |  |  |  |  |
| **To evaluate the prevalence of co-infections of selected STIs/BV: gonorrhea, chlamydia, syphilis, trichomoniasis, HSV-2, and/or BV** | **All studies** |  | **√** |  | **√** |
| **To evaluate the incidence of co-infections among the STIs: chlamydia, gonorrhea, and HSV-2** | **All studies** |  | **√** |  | **√** |
| **Sensitivity Analysis** |  |  |  |  |  |
| **To evaluate the prevalence of gonorrhea, chlamydia, syphilis, and BV based on the type of diagnostic criteria** | **All studies** |  | **√** |  | **√** |

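### Section 3.6 lets the HIV-discordant-couple studies be placed in a population-type stratum after their own STI/BV estimates have been seen, so the outcome helps define the stratum

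*Protocol*

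**What the plan says.** Section 3.6 presents the strata as fixed beforehand: "for each STI/BV we plan to stratify results according to pre-specified characteristics". It defines the main one by design: "Population types (based on overall study population enrolled) will be defined as higher-risk or clinic/community-based populations".

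For studies of HIV-negative women in discordant couples it then sets a different procedure. They are analysed on their own first. Next: "STI/BV specific estimates reviewed, and if appropriate (based on comparison with estimates from other populations), will be included in either the higher-risk strata". The clinic stratum is named as the other option. The last branch reads: "If not appropriate, estimates from these studies will be presented separately". The section also offers a subject-matter argument, that "their risk for STI/BV may be similar to clinic/community-based populations given that they are in a stable relationship", but does not turn it into the rule.

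Table 1 gives these datasets a category of their own, HIV-discordant couples. Table 5 lists only "higher-risk or clinic/community-based populations" for population type, in both its prevalence and its incidence block. Section 3.7 uses the same two levels: "STI co-infection estimates will be estimated by population type". Section 5.2.1 pools to an "overall estimate of prevalence and incidence across studies by population-type". None of the sensitivity analyses in section 5.3 varies the placement.

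**The concern.** A stratum should be defined by something other than the quantity it is used to summarise. Here four datasets may be placed by how their prevalence or incidence compares with that of the other populations. Moving a dataset towards the group it resembles tends to widen the observed gap between the groups.

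This matters because population type is a first-level stratifier and the level at which the two-stage analysis pools, and because section 2 names differences by population type as something to be investigated.

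Two gaps add to it. Nothing requires one placement across infections, or across prevalence and incidence. And couples who end up separate have no category in Table 5 or section 3.7.

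**Working it through.** **Inputs from Table 1 (Included N).**
- Higher-risk, 7 rows, all Eastern Africa: 1,270 + 414 + 978 + 781 + 418 + 873 + 1,018 = 5,752.
- Clinic/community, 15 rows: Eastern 2,201 + 380 = 2,581; Southern 6,846; South Africa 20,463; total 29,890.
- Discordant couples, 4 rows: 913 (15a) + 214 (15b) + 138 (15c) + 774 (16b) = 2,039.

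**The plan's own figure.** 5,752 + 29,890 + 2,039 = 37,681, which agrees with the approximately 37,000 in the Study Summary (1.8% higher).

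**Share of the placement.**
- Overall: 2,039 / 37,681 = 5.4%.
- Added to all clinic/community: 2,039 / (29,890 + 2,039) = 6.4%.
- Added to all higher-risk: 2,039 / (5,752 + 2,039) = 26.2%.
- Eastern Africa has 913 + 774 = 1,687 discordant women. In the clinic stratum they are 1,687 / (2,581 + 1,687) = 39.5%, and 2 of 4 datasets. In the higher-risk stratum they are 1,687 / (5,752 + 1,687) = 22.7%.
- Southern Africa and South Africa have no high-risk row. Placing couples there as higher-risk would create strata made only of 214 and 138 discordant women.

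These sums count all enrolled women; the numbers tested for each infection will be smaller.

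**Illustrative simulation.** Its inputs are assumptions, not protocol figures: true prevalence 10% in every population, between-study SD 0.3 on the logit scale, Table 1 sizes, DerSimonian-Laird pooling, 20,000 runs. The entry is how often |higher-risk minus clinic| / SE exceeds 1.96 when there is no true difference.

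| Placement of couples | All regions | Eastern Africa |
|---|---|---|
| Kept apart | 7.8% | 16.7% |
| Fixed in clinic | 7.9% | 9.5% |
| Always merged, as a block, into the nearer stratum | 11.3% | 22.8% |
| Always merged, each row into its nearer stratum | 19.7% | 29.9% |

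Other runs of the block scenario in all regions gave 11% to 12%. The excess over 5% in the first two rows comes from having few studies, not from the placement rule. Row-by-row placement is not stated in the protocol, but is not excluded either.

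**With the separate branch allowed.** Suppose the block is merged only when it differs significantly from exactly one of the two strata, and then joins the other (an assumed rule). Rejection is then about 9% (all regions) and 21% (Eastern Africa), and the couples stay apart in about 89% and 80% of runs. The excess over keeping them apart falls to about 2 and 4 percentage points.

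**I².** Averaged over the two strata, I² in all regions is 85.8% with couples apart, 85.3% with block merging and 85.3% with fixed clinic placement. In Eastern Africa it is 65%, 68% and 77% respectively.

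**The case against.** The strongest defence is that the step is disclosed and cautious. The couples are analysed separately first, merged only if judged appropriate, and otherwise shown on their own; Table 1 already sets them apart. The other 22 of 26 rows are classed by recruitment setting, and Table 5's all-studies estimates do not depend on the placement. The study estimates rates and specifies no 5% test of higher-risk against clinic.

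For incidence the reach is smaller still. Table 3, which is marked as still to be updated, shows no chlamydia or gonorrhea follow-up for study 15 and only prevalent HSV-2 results. On those entries only 16b (774 women) could contribute to incidence of these three infections.

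All of that stands and limits the size of the problem. It does not remove it: the choice among the three branches is itself made on the estimates, with no stated criterion.

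Four stronger readings are tempting but not supported.
- That the couples are always assigned to the stratum they resemble. The text has the separate branch.
- That I² and pooled intervals become too favourable. No material fall in I² appears against keeping the couples apart, and in Eastern Africa block merging raises it slightly. The effect on the intervals was not calculated.
- That the same women will count as higher-risk for one infection and clinic for another, leaving co-infection without a denominator. The review is infection-specific, but the text only leaves different placements open. Section 3.7 ties its strata to the enrolled population and its denominators to women tested for both infections.
- That the population-type strata as a whole lose their meaning. Four datasets are affected.

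**Conclusion.** The point holds in limited form. Section 3.6 contains an outcome-dependent rule that conflicts with its own claims of pre-specification and of a design-based population type, and Table 5 and section 3.7 cannot hold one of its three results.

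The expected harm is an overstated higher-risk versus clinic contrast. It is modest over all regions and concentrated in Eastern Africa, the only region with both strata. The simulated rates show direction and rough size only: they rest on the assumed prevalence and SD, on a comparison the protocol does not specify and, for the larger figures, on merging every time.

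This should be fixed, and before any estimates are reviewed, but it does not undermine the plan as a whole.

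**What to change.** Delete the review-and-merge step in section 3.6. State one placement, chosen on design grounds before estimates are seen, and the same for every STI/BV and for both prevalence and incidence.

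A straightforward choice is to make Table 1's third category the main analysis and add clinic plus discordant couples to section 5.3 as a pre-set sensitivity analysis. The reverse is equally free of circularity and follows the section's own argument about stable relationships. Either way, always report the discordant-couple estimates separately, and bring Table 5 (prevalence and incidence blocks) and section 3.7 into line; the supplemental stratification tables may also need the change.

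The cost is a few sentences and table rows, with no new data. Keeping the couples apart leaves single-dataset discordant strata in Southern Africa (214 women) and South Africa (138), and takes up to 2,039 women out of the two main strata. Fixed clinic placement avoids that, but mixes two populations in Eastern Africa, where the couples would be about 40% of the stratum.
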